### Sample size

The sample size calculation was performed using PASS (version 2021) with the “Comparison of two independent sample rates” calculation module. A power of 80% and an alpha level of 0.025 for a one-sided test and a superiority test were used. Based on a previous study by our team [22], the flare rates of acute gouty arthritis after 12 weeks of placebo treatment were 63.2%, and for the group treated with the QTF was 38.5%. Calculations yielded sample sizes of N1 = N2 = 61 for both the intervention and control groups, considering a dropout rate of 20%. In total, 144 patients with intermittent gout will be included, with 72 patients in both the intervention and control groups.

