#### Secondary outcomes.

1. The Time span from patient’s enrollment to the first occurrence of gout flares (in days); 2. Duration of gout flares (in days); 3. Health Assessment Questionnaire Disability Index (HAQ-DI) for quality-of-life assessment; 4. Changes in visual analog scale (VAS). 5. Rate of achieving target uric acid levels (Compliance rate = number of eligible patients/total number of patients under observation x 100%; Standard: Gout treatment achievement is defined as lowering serum uric acid levels to below 360 umol/L through the use of uric acid-lowering medications). Outcomes 1–4 will be recorded at weeks 6, 12, 24, and 48. Outcome 5 will be recorded at weeks 12, 24, and 48.

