### Statistical analysis

The statistical analysis for this trial will be conducted based on the Per-Protocol (PP) and Intent-to-Treat (ITT) data, conducted by Jiangsu Famous Medicine Co., Ltd., situated in Nanjing, China. Different analysis methods will be employed depending on the type of data measurement or counting.

For the primary outcome, the number of gout flares in each group will be compared using t-tests or Wilcoxon rank-sum tests, with center effects controlled through covariance analysis. For count data, such as time span to the first occurrence of gout flares, duration of acute gouty arthritis recurrence, pain visual analog scale score, HAQ-DI, and safety analysis indicators (like routine blood tests), the same methods will be applied. Measurement data, including the recurrence rate of acute gouty arthritis and the incidence of adverse events, will be analyzed using chi-square tests or Fisher’s exact tests, with center effects controlled through binary or multinomial logistic regression analysis. All hypothesis tests in this study will be two-sided, with a significance level of 0.05. Differences will be considered statistically significant when p < 0.05. SAS version 9.4 will be used for all statistical analyses.

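### HAQ-DI is scored at four visits but assigned a test that takes one value per patient, so earlier scores cannot help if dropout depends on them

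*Protocol article*

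**What the plan says.** Under Secondary outcomes, the third item is the "Health Assessment Questionnaire Disability Index (HAQ-DI) for quality-of-life assessment", and the same section states that "Outcomes 1–4 will be recorded at weeks 6, 12, 24, and 48". Each patient can therefore contribute up to four scores after randomization.

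Under Statistical analysis, the number of flares is to be "compared using t-tests or Wilcoxon rank-sum tests, with center effects controlled through covariance analysis". HAQ-DI is then attached to that sentence: for "HAQ-DI, and safety analysis indicators (like routine blood tests), the same methods will be applied". The analyses are "based on the Per-Protocol (PP) and Intent-to-Treat (ITT) data", and "All hypothesis tests in this study will be two-sided, with a significance level of 0.05".

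The only dropout figure is in the Sample size section, where the flare-rate calculation is described as "considering a dropout rate of 20" per cent.

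The article names no longitudinal model and no key visit for HAQ-DI. It does not say how missing scores are handled.

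**The concern.** A t-test or rank-sum test needs one number per patient. With four scores per patient there are three ways to use it: at each visit separately, on a summary of the visits, or on all scores pooled. Pooling would break the independence that the test assumes. The separate-visit reading is the most natural, though the article does not state it. Adjusting for centre by covariance analysis does not change this, because centre carries no information from a patient's earlier visits.

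A patient who leaves after week 6 has a week-6 score that says something about the missing later ones. A single-visit analysis of observed scores discards it. If leaving is related to the earlier score, the patients seen later are a selected group, and the difference between arms among them need not equal the difference among all randomized patients. What is at stake is the size and power of a secondary result.

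**Working it through.** **Inputs from the protocol article.** 72 patients per arm, 20% dropout, HAQ-DI at four visits, two-sided 0.05. The article gives no HAQ-DI effect, standard deviation (SD), between-visit correlation or dropout mechanism, so those below are assumptions.

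**The plan's own figure.** There is none for HAQ-DI. The flare-rate sample size ("A power of 80% and an alpha level of 0.025 for a one-sided test and a superiority test were used") reproduces with unpooled variance:

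(1.960 + 0.842)² × (0.632 × 0.368 + 0.385 × 0.615) / (0.632 − 0.385)² = 60.4, rounded up to 61 per arm.

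The step to 72 fits about 15% loss (61/0.85 = 71.8). At 20% it would be 61/0.80 = 76.25, or 77. That is a separate matter. Here it means only that 20% loss from 72 leaves 72 × 0.80 = 57.6, about 58 per arm.

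**Step 1: loss of numbers alone.** The difference detectable with 80% power, in SD units, is (1.960 + 0.842) × √(2/n).

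- n = 72: 0.47 SD; power for 0.5 SD is 85%.
- n = 58: 0.52 SD; power for 0.5 SD is 77%.

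This is lost precision, not bias.

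**Step 2: week 12, dropout driven by the week-6 score.** 5,000 simulated trials per scenario; correlation 0.6; 20% leave after week 6; logistic slope 0.7 or 1.2 per SD of the week-6 score, with the same rule in both arms.

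| True difference (SD) | Completer estimate, slope 0.7 / 1.2 | Likelihood using week 6 | Completer power | Likelihood power |
|---|---|---|---|---|
| −0.30 | −0.291 / −0.270 | −0.303 / −0.295 | 31-34% | 37-38% |
| −0.50 | −0.482 / −0.460 | −0.500 / −0.502 | 71-73% | 79% |

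Shrinkage is 1 − 0.291/0.30 = 3% and 1 − 0.270/0.30 = 10% in the first row, and 1 − 0.482/0.50 = 4% and 1 − 0.460/0.50 = 8% in the second. With no true effect, both methods reject in 4.8-5.5% of trials, so the planned test is valid under the null hypothesis.

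With scores piled up at zero, the relative shrinkage was larger. Power was 33-50% for completers against 46-61% for the likelihood model, and type I error held.

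**Step 3: week 48, other dropout mechanisms.** 1,000 trials per scenario; baseline plus four visits; true difference 0.50 SD; 20-25% gone by week 48; Monte Carlo error about 0.006.

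| Who leaves | Completer estimate at correlation 0.3 / 0.5 / 0.7 |
|---|---|
| Completely at random | 0.50 / 0.50 / 0.50 |
| Worse patients, same rule in both arms | 0.49 / 0.48 / 0.48 |
| Worse patients in control; random in active | 0.42 / 0.38 / 0.35 |
| Worse in control, better in active | 0.36 / 0.29 / 0.22 |
| Better in control, worse in active | 0.65 / 0.76 / 0.83 |

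A likelihood estimate using all visits stayed at 0.49-0.51 in every row. It was given a baseline score, which the article's text does not confirm is collected. Under random dropout its gain was small: the SD of the estimate was 0.199 against 0.202, 0.175 against 0.182 and 0.168 against 0.178 for the three correlations.

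**The case against.** The strongest case against is that the article is silent on the points that would make this a fault. A reader might infer that HAQ-DI is tested visit by visit on whoever is still present. The article does not say so: it names ITT as well as per-protocol data, and an analysis plan not shown may specify imputation or a key visit. That stands, and missing-data handling is not counted as an omission here. What remains is that the test itself is stated and uses one value per patient.

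A reader might also infer that 20% dropout attenuates the effect. It does not by itself. Random dropout gives no bias, the same rule in both arms gives almost none at week 48, and arm-specific dropout can shrink or inflate the difference. The exit reasons listed (adherence, medication outside the protocol, unblinding, adverse events, patient request, loss to follow-up) could plausibly relate to disability, but the article does not link them to HAQ-DI.

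The normal-score simulations can be questioned too. Patients enter between flares with a pain score of zero, so HAQ-DI may cluster at zero. The likelihood model kept its advantage there when dropout followed the week-6 score. Under random dropout with clustered scores, the Wilcoxon test was slightly ahead. That supports keeping the Wilcoxon test in the plan.

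Finally, the 20% is a planning allowance with no timing. Placing all of it between weeks 6 and 12 probably overstates loss at week 12.

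**Conclusion.** The concern holds in a limited form. The article fixes a one-value-per-patient test for an outcome measured four times, and a cheap alternative would use the scores already collected. The gain depends on an unknown dropout mechanism. It is negligible if dropout is random. It is modest at week 12 if dropout follows the week-6 score under one rule in both arms: about 3-10% shrinkage and roughly 3 to 8 percentage points of power with normal scores. It could be large, in either direction, if the two arms lose different kinds of patient.

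These sizes rest on assumed effects of 0.3 or 0.5 SD, the stated correlations and slopes, and dropout that depends only on observed scores. The planned test keeps its type I error in the scenarios checked. HAQ-DI is secondary, so the trial's primary conclusion does not change. This is a worthwhile improvement, not an error that must be corrected before the trial can be interpreted.

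**What to change.** In the Statistical analysis section, take HAQ-DI out of the group that follows the primary outcome's method. Analyse it with one mixed model for repeated measures containing arm, visit, arm-by-visit interaction and centre, with an unstructured covariance across visits, and add baseline HAQ-DI if it is collected. Include all randomized patients with at least one post-baseline score. Name the week-12 contrast, at the end of the 12-week treatment period, as the main HAQ-DI result, and report the other visits from the same model. Keep the planned Wilcoxon test as a sensitivity analysis, since scores may pile up at zero.

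The cost is a few lines of SAS code and no new data. The downside is reliance on data missing at random and roughly normal residuals. The Wilcoxon test checks the second assumption but not the first. If a full analysis plan already specifies such a model, the article's sentence only needs to be brought into line with it.

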In recent years, Traditional Chinese Medicine (TCM) has been increasingly recognized for its effectiveness [19]. When combined with chemical drugs, TCM has shown enhanced efficacy in halting disease progression compared to chemical drugs alone [20]. Research has indicated that the aqueous extract of Tongfengkang not only possesses a significant anti-inflammatory effect on gouty arthritis (GA) but also lowers blood urate concentration [21]. Previous studies conducted by our team have demonstrated that Qu-zhuo Tong-bi formula (QTF) granules are effective in reducing blood urate levels and acute gout flares, with no adverse reactions reported even after prolonged use. However, these studies did not include follow-up after treatment [22]. Despite these promising results, there remains a gap in traditional Chinese medicine (TCM) research concerning the prevention of gout flares during urate-lowering therapy (ULT). To address this gap, we propose a multi-center, randomized, double-blind, placebo-controlled, parallel-group clinical trial. This study aims to investigate whether QTF granules can reduce the frequency and duration of acute gout flares associated with ULT and prolong the time to flare. Additionally, we will address the existing research gap by including a 48-week follow-up period after treatment to evaluate the long-term effects of QTF granules. The aim is to identify a safe and effective new therapeutic medication for reducing acute gout flares in the early stages of ULT in gout patients, providing valuable insights and a foundation for TCM clinical management and novel drug development.

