#### Safety outcomes.

Patients undergo pre- and post-treatment examinations, including blood routine, urine routine, stool routine, liver and kidney function tests (ALT, AST, BUN, Cr, SUA), and electrocardiography, to assess the safety of the interventions in this study. The blood, urine, and stool specimens collected from the patients after completion of the tests are to be disposed of by medical staff according to regulations.

We employ the Common Terminology Criteria for Adverse Events (CTCAE) version 5.0 from the National Cancer Institute of the United States to document the severity of adverse events, categorized from grades 1–5 [25]. According to the classification system devised by the Drug Adverse Reaction Monitoring Center of the Chinese Ministry of Health, adverse events are classified into five levels: “definitely related, probably related, possibly related, probably unrelated, definitely unrelated.” The first three levels are deemed to be associated with the investigational medication [26]. Any adverse events during treatment will be documented based on severity and their causal assessment outcomes. In the event of serious adverse events during the study, immediate measures must be taken and reported to the research design unit’s project manager and ethics committee, which will determine whether to proceed or terminate the study. All adverse events should be monitored until appropriately resolved or stabilized.

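### Safety is an aim, but the only between-arm safety analysis stated is a significance test at two-sided 0.05, which with 72 per arm says little about uncommon harms

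*Protocol article*

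**What the plan says.** The abstract names safety beside effectiveness as what the trial evaluates. The Introduction goes further: "The aim is to identify a safe and effective new therapeutic medication for reducing acute gout flares in the early stages of ULT in gout". The Safety outcomes section lists blood, urine, stool, liver and kidney tests and electrocardiography before and after treatment "to assess the safety of the interventions in this study".

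The Statistical analysis section then fixes how the arms are compared:

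- **Adverse events:** "Measurement data, including the recurrence rate of acute gouty arthritis and the incidence of adverse events, will be analyzed using chi-square tests or Fisher’s exact"; logistic regression is named to control centre effects.
- **Laboratory values:** for "safety analysis indicators (like routine blood tests), the same methods will be applied", meaning the t-test or Wilcoxon rank-sum test named for the primary outcome.
- **Criterion:** "All hypothesis tests in this study will be two-sided, with a significance level of 0.05".

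The Sample size section rests on flare rates alone: "the flare rates of acute gouty arthritis after 12 weeks of placebo treatment were 63.2" per cent and "for the group treated with the QTF was 38.5" per cent.

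Other safety provisions exist. Events are graded by CTCAE v5.0 and assessed for causality on five levels. Serious events go to the project manager and ethics committee, who may end the study. A data monitoring committee audits the data and makes an interim assessment meant to cover effectiveness and safety.

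**The concern.** Chi-square, Fisher, t and Wilcoxon tests ask whether a difference can be shown. They suit an efficacy claim. For safety, the favourable result is that no difference is shown, and such a test cannot tell absence of harm from too few patients. The trial was sized for a flare difference of 63.2 − 38.5 = 24.7 percentage points, far larger than most adverse-event differences of interest.

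Laboratory values raise a second problem. If liver or kidney harm takes the form of large rises in a few patients, a comparison of group means or ranks is aimed at the wrong quantity. The grading needed to count those patients is already part of the protocol.

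What is at stake is the safety statement the trial can make. A non-significant p-value and a confidence interval from the same data can support quite different conclusions.

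**Working it through.** **1. The plan's own figure.** Inputs from the Sample size section: 63.2%, 38.5%, one-sided alpha 0.025, power 80%. With the unpooled two-proportion formula,

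n = (1.960 + 0.842)² × [0.632 × 0.368 + 0.385 × 0.615] / 0.247² = 7.849 × 0.4694 / 0.0610 = 60.4, rounded up to 61 per arm.

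This reproduces the stated 61. No adverse-event rate enters the calculation.

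**2. Power for a doubling of an adverse-event rate.** Inputs: 72 per arm (Sample size) and two-sided 0.05 (Statistical analysis). The article gives no background rate, so the control rate is an assumption and is shown over a range. Method: enumerate all pairs of binomial counts and add the probabilities of those where the test rejects in the direction of harm.

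| Control v QTF (assumed) | Fisher, 72 per arm | Chi-square, 72 per arm | Fisher, 58 per arm | Chi-square, 58 per arm |
|---|---|---|---|---|
| 5% v 10% | 12% | 21% | 8% | 17% |
| 10% v 20% | 32% | 39% | 24% | 33% |
| 15% v 30% | 51% | 59% | 41% | 50% |
| 20% v 40% | 70% | 76% | 59% | 66% |
| 25% v 50% | 84% | 88% | 74% | 80% |

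The 58 is 72 × 0.80 = 57.6, rounded up, using the stated 20% dropout.

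Normal-approximation check for 10% v 20% at 72 per arm: z = [0.10 × √72 − 1.960 × √(2 × 0.15 × 0.85)] / √(0.10 × 0.90 + 0.20 × 0.80) = (0.849 − 0.990) / 0.500 = −0.28, which is a power of 39%.

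At 72 per arm, power passes 50% at a control rate of about 12.5% (chi-square) to 15% (Fisher). For 80% power, 5% v 10% would need 435 per arm and 10% v 20% would need 199.

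**3. The same data as a test and as an interval.** Take 14/72 v 7/72 patients with an event (19.4% v 9.7%), as an illustration.

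- Fisher p = 0.155 and chi-square p = 0.098. Both are non-significant.
- Wilson limits are 0.1195 to 0.3003 and 0.0479 to 0.1874.
- Newcombe upper limit: 0.0972 + √[(0.3003 − 0.1944)² + (0.0972 − 0.0479)²] = 0.214.
- Newcombe lower limit: 0.0972 − √[(0.1944 − 0.1195)² + (0.1874 − 0.0972)²] = −0.020.

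The excess is +9.7 points (95% CI −2.0 to +21.4). With equal counts, 7/72 v 7/72, the interval is ±√[(0.1874 − 0.0972)² + (0.0972 − 0.0479)²] = ±10.3 points.

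**4. Laboratory values.** For a shift of the whole group, 80% power at 72 per arm needs (1.960 + 0.842) × √(2/72) = 0.47 SD. The t-test has about 85% power for 0.5 SD and about 32% for 0.25 SD.

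For harm in a few patients, assume ALT is log-normal with median 25 and log-SD 0.45, and that each QTF patient has a 5% chance of a fourfold rise (on average 0.05 × 72 = 3.6 patients) while no placebo patient does. By simulation, power is about 19% for the t-test on untransformed values and about 8% for Wilcoxon.

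**The case against.** Three stronger readings are tempting, and the article supports none of them.

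- **A reader might infer that non-significance will be taken as safety.** The article never says so. Its remark that traditional Chinese medicine is relatively safe is background in the Discussion, not a conclusion from these tests.
- **A reader might infer that the p-value is the only safety provision.** It is not. CTCAE grading, causality assessment, the serious-event rule and the data monitoring committee are all stated. What can be said is that the p-value is the only between-arm statistical analysis stated for safety.
- **A reader might infer that the trial would usually miss any doubling of harm.** That depends on a background rate the article does not give. If overall adverse-event incidence on placebo is 20% or more, a doubling would more likely be found than missed.

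It can also be argued that intervals and grade-shift tables belong in a full protocol or analysis plan that is not shown, and that the authors already call the trial exploratory and small. The first argument would defeat a complaint that intervals are merely absent. Here the article itself names the tests and the criterion, so the suitability of that stated choice can be judged. The logistic models could yield intervals, but they are stated only as control for centre. The admitted small sample does not narrow the safety aim; it is a further reason to show the uncertainty.

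The ALT scenario is invented, and a group shift of 0.5 SD would be well detected. The laboratory part therefore concerns only harm concentrated in few patients. These limits on the point stand.

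**Conclusion.** The point holds in this limited form: safety is an aim, while the stated between-arm safety analysis seeks differences at two-sided 0.05 and cannot support a safety conclusion for uncommon events. At 72 per arm a doubling is missed more often than not when the control rate is below about 12–15%. It is missed in 79–88% of trials for 5% v 10% and in 61–68% for 10% v 20%. For 20% v 40% it is missed in only 24–30%.

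All these rates are assumptions. The one hint in the article, that earlier QTF work reported no adverse reactions, points to low rates but does not establish one. The 8–19% power for concentrated ALT rises depends on the distribution assumed.

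This is a worthwhile, inexpensive improvement to the analysis. It is not a threat to patient protection or to the efficacy result.

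**What to change.** In the Statistical analysis section, separate safety from the general 0.05 criterion:

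1. Report the number and percentage of patients per arm with any, treatment-related and serious adverse events, each with the risk difference and its 95% confidence interval (Newcombe or exact).
2. For laboratory tests with CTCAE v5.0 grades (ALT, AST, creatinine, blood counts), report in the same way the number of patients whose grade worsens from baseline. Keep the mean or rank comparisons as descriptive.
3. State that any safety conclusion rests on the upper confidence limit and is confined to the size of harm that limit excludes, and that a non-significant p-value will not be offered as evidence of safety.

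This changes wording only. Adverse events, CTCAE grading and laboratory values before and after treatment are already planned, so no visits, patients or tests are added. It adds no power. The price is a less favourable safety statement, as the ±10.3 points for equal counts of 7/72 shows.

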### Inclusion criteria

All participants must meet the following criteria:

Meet the above diagnostic criteria and be in the gout intermission stage;TCM diagnosis indicates syndrome of spleen deficiency with dampness obstruction;Serum urate level ≥7 mg/dL (420μmol/L);Aged between 18 and 80 years (inclusive of boundary values), any gender;Having not received urate-lowering drugs such as allopurinol, benzbromarone, or febuxostat in the past month;Relief of gouty flare symptoms (VAS score = 0) for more than 1 week;Acute gout flare≥2 in the past year;Willing to undergo treatment and sign informed consent.

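### The analysis rule that by data type covers the uric acid target rate adjusts for center only and leaves out pre-treatment serum urate, which is already collected; the cost is some efficiency on a secondary endpoint

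*Protocol article*

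**What the plan says.** The Statistical analysis section assigns methods by type of data. Its rule for rates opens with "Measurement data, including the recurrence rate of acute gouty arthritis and the incidence of adverse events" and says that these "will be analyzed using chi-square tests or Fisher’s exact tests, with center effects controlled through binary or multinomial logistic regression analysis". The label for the data type is unusual, but the two examples show that rates are meant. Center is the only factor named, and the section names no baseline covariate for any outcome.

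Secondary outcome 5 is "Rate of achieving target uric acid levels". The Secondary outcomes section makes it a yes/no result: "Gout treatment achievement is defined as lowering serum uric acid levels to below 360 umol/L". It adds that "Outcome 5 will be recorded at weeks 12, 24, and 48".

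Three other places bear on the point:

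- **Inclusion criteria:** entry requires a serum urate of at least 420 umol/L, with no upper limit.
- **Safety outcomes:** serum uric acid is among the laboratory tests done before and after treatment.
- **Intervention:** both arms receive the same stipulated febuxostat dose.

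**The concern.** The target is an absolute value, so a patient's starting urate fixes how far it has to fall. If follow-up urate is correlated with baseline urate, part of the variation in who reaches target is explained by a number already on the case report form. A test that ignores it treats that part as noise. Center adjustment does not recover it, and the Randomization and blinding section names no urate stratum.

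At stake is the precision of the comparison on whether QTF adds to urate lowering. The Introduction and Discussion cite prior evidence of such an effect as part of the rationale, and the authors call their own sample small. The primary outcome is not affected.

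**Working it through.** **1. The plan's own figure.** The protocol gives no power or sample size for the target rate. Its only calculation is for the 12-week flare rate: 63.2% v 38.5%, one-sided 0.025, power 80%. The unpooled formula reproduces it:

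n = (1.960 + 0.842)² × (0.632 × 0.368 + 0.385 × 0.615) / (0.632 − 0.385)² = 60.4, so 61 per arm.

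**2. Patients available for outcome 5.** The trial randomizes 72 per arm. With the stated 20% dropout, 72 × 0.8 = 57.6, about 58 per arm. I use 58 (after dropout) and 72 (all randomized).

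**3. Starting distance from target.** At the entry floor the required fall is (420 − 360)/420 = 14%. For two illustrative starting values, which are not from the protocol, it is (430 − 360)/430 = 16% and (650 − 360)/650 = 45%. This is arithmetic about where patients start. It does not show how well baseline predicts success.

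**4. Power with and without baseline urate.** Assumptions, none given in the protocol:

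- baseline urate normal (mean 500, SD 80), cut at 420;
- latent follow-up urate correlated rho with baseline;
- follow-up cut-offs set to give the assumed target rates in each arm;
- four equal centers with no center effect.

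Tests are likelihood-ratio tests for treatment at two-sided 0.05, with 2,000 simulated trials per setting. Each cell shows power with center only → power with center and baseline urate (gain in points).

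| Per arm | Target rates | rho 0 | rho 0.3 | rho 0.5 | rho 0.7 |
|---|---|---|---|---|---|
| 58 | 40% v 60% | 0.597 → 0.601 (+0.4) | 0.5895 → 0.6285 (+3.9) | 0.5965 → 0.6945 (+9.8) | 0.568 → 0.7515 (+18.35) |
| 58 | 45% v 70% | 0.790 → 0.791 (+0.1) | 0.793 → 0.816 (+2.3) | 0.7935 → 0.8605 (+6.7) | 0.8015 → 0.9325 (+13.1) |
| 72 | 40% v 60% | 0.694 → 0.690 (−0.4) | 0.6945 → 0.7145 (+2.0) | 0.682 → 0.7595 (+7.75) | 0.691 → 0.834 (+14.3) |
| 72 | 45% v 70% | 0.870 → 0.8705 (+0.05) | 0.867 → 0.889 (+2.2) | 0.8715 → 0.930 (+5.85) | 0.8685 → 0.9655 (+9.7) |

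The plain chi-square test had nearly the same power as the center-only model. At 58 per arm, 40% v 60% and rho 0.5, for example, it was 0.5915 against 0.5965.

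**5. Simulation error.** A power near 0.6 from 2,000 runs has a standard error of √(0.6 × 0.4/2000) = 0.011, about 1 point. A second run of the same design gave gains of about 2 points at rho 0.3, 5 to 8 at rho 0.5 and 10 to 17 at rho 0.7. A repeat with 5,000 runs per setting agreed with that second set to within about a point, so I use it as the headline.

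**6. Validity.** With 50% at target in both arms, the rejection rate was between 0.04 and 0.06 for all three tests: chi-square, center only, and center with baseline urate.

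**The case against.** The best case against is that nothing here is false. An article gives one paragraph on methods, and the covariates for a secondary endpoint often sit in the statistical analysis plan, which is not shown. The sentence on rates does not name the target rate, nor does it say that no other covariate may enter. Much of this stands. Placing outcome 5 under the rule is an inference from its data type, and an unseen plan could add covariates. What remains is that the protocol does state a method and an adjustment, the rule fits this outcome, and no other rule does. The point is an improvement to that stated method.

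Three stronger readings are tempting, and the documents do not support them:

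- **Baseline urate is a strong predictor of success.** The protocol reports no correlation, target rate or baseline distribution. Only the starting distance is known. The entry cut at 420 umol/L may also lower the correlation within the trial.
- **Chance imbalance in baseline urate undermines the comparison.** Allocation is random 1:1, and the test's error rate already allows for chance imbalance. Step 6 found no inflation.
- **The trial has 61 evaluable patients per arm for this endpoint.** That is the calculated requirement for the flare rate. The stated enrolment and dropout leave about 58.

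It is also fair that the trial was not sized for this outcome and that its authors call it exploratory.

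**Conclusion.** The point holds as a minor gain in efficiency on a secondary endpoint. The planned test is valid, and no primary conclusion depends on the change. With 58 to 72 per arm, adding pre-treatment urate to the center-only model is worth about 2 power points at rho 0.3, 5 to 8 at rho 0.5 and 10 to 17 at rho 0.7, and costs nothing material at rho 0. These figures rest on the assumed target rates (40% v 60% and 45% v 70%), the assumed baseline distribution and the assumed rho. The direction does not depend on the exact values as long as rho is above zero; the size does.

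**What to change.** In the Statistical analysis section, name the uric acid target rate and give its analysis: logistic regression with treatment, center and continuous pre-treatment serum urate. Apply it at each visit with a serum urate value, that is weeks 12 and 24, and week 48 where a value is obtained, since that visit is held by phone or WeChat. Report the standardized (marginal) risk difference with its 95% CI, and keep the chi-square result as a supporting figure.

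The cost is one sentence of wording, set before unblinding, with no new data. The small downside is that the adjusted odds ratio is conditional on baseline urate and so not directly comparable with the crude one. Reporting the standardized risk difference resolves this.
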